### Quantitative analyses

There will be a single analysis at study end (there is no opportunity for any interim analyses given the cross-over design) although an independent data monitoring committee will monitor study progress and any safety issues. This will follow the intention-to-treat principle and will use a hierarchical model appropriate for the specific outcome. For the primary outcome, this will be a mixed-effects logistic regression, using the hierarchical model approach as recommended by Turner *et al* for a cluster cross-over design.^21^ We will prespecify any individual level (or cluster level) covariates that we intend to adjust for, and the comprehensive statistical analysis plan will specify the sensitivity type analyses that will explore how robust the findings are to any missing data at the cluster level (probably unlikely) and the individual level (expected to be substantial for the patient reported outcomes at 4 months). As well as the usual assumption of missing at random, we will try to explore possible mechanisms for non-ignorable (informative missingness) at the individual level, which may well be operating in this context. Subgroup analyses will explore the possible effect modification by LARC (most effective contraceptive methods) versus non-LARC vs no use of contraception.

### Qualitative and mixed-methods process evaluation analyses

All process data will be analysed independently of the outcome data and, importantly, documented before the outcomes are known. Qualitative analysis of in-depth interviews will be recorded and transcribed verbatim. Transcription and analysis (proceeding case by case) will start with the first interview and be ongoing during the course of data collection, allowing for emergent themes to be identified and explored in future interviews. The transcripts will be read repeatedly and coded for analysis. Data management will be assisted by the software, QSR NVivo V.10. Analysis will be undertaken using ‘Framework Analysis’ a method of proven validity and reliability where data are coded, indexed and charted systematically, then organised using a matrix or framework.^22^ Constant comparison will be carried out to ensure that the analysis represents all perspectives and negative (‘deviant’) cases.

The multisource process evaluation will be synthesised to address the three key process evaluation questions: (1) what was delivered, (2) how it was delivered and (3) what role context may have had in shaping the delivery/outcomes

#### Economic evaluation

An economic evaluation will be undertaken comparing the intervention and control arms in a cost-effectiveness analysis. A trial-based analysis will be followed by the construction of a decision model to extrapolate future costs and benefits beyond the completion of the trial. The overall perspective used will be that of the health system. Costs will include the pharmacist training to provide POP, direct and indirect costs of health service use, and the provision and dispensing of POP. We will compare the costs to the NHS in the intervention and control arms. To account for differences in the numbers of women in the two arms, we will compare the cost per woman in each arm. In the control arm, the costs are (1) cost of EC, (2) cost of pharmacist provision of EC, (3) cost of abortions. In the intervention arm, the costs are in addition to these (4) the cost of the POP, (5) cost of pharmacist training to provide POP and (6) cost of pharmacist provision of POP. The costs (1) and (2) are the same in both groups and so the extra cost of the intervention will be the sum of (4), (5) and (6). The cost per women who has an abortion is the same in both groups except that we hypothesise that the abortion rate will be lower in the intervention group. We can then state the outcome as conventional incremental cost-effectiveness ratio that is, for every £100 spent on the intervention results in x fewer abortions for a savings of £Y. If Y is greater than 100 then the intervention is cost-effective. We will examine the sensitivity of the outcomes to variations in the costs of 4, 5 and 6.

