## Introduction

Unintended pregnancy is widely perceived as a major public health problem. Unintended pregnancy commonly ends in abortion and the UK has among the highest abortion rates in Europe.^1^ In 2017, almost 200 000 pregnancies ended in induced abortion.^2 3^ Unintended pregnancy also ends in childbirth; around 10% of UK births are unintended and 25% mistimed.^4^ Unintended pregnancy is costly to the National Health Service (NHS) (estimated to cost over £1 billion annually)^5^ and can be distressing for women. Unintended pregnancies are more common in young women from deprived backgrounds, contributing to widening health inequalities for both mother and baby, and their families.^2 3^ Unintended childbirth can have both socioeconomic consequences for women and their families and mental health consequences.^6^

Oral emergency contraception (EC) prevents pregnancy in individual women following unprotected sex or contraceptive accidents. EC is only effective if taken before ovulation as it works by inhibiting or delaying ovulation.^7^ Since EC became available from pharmacies in the UK without the need for a prescription, there has been a change in the pattern of access such that women who seek EC now choose to obtain this from a pharmacy rather than a contraceptive provider such as a general practitioner (GP) or sexual and reproductive health (SRH) service.^8^ Although trials have shown that this facilitates access to EC and increases use, they have failed to show that this reduces unintended pregnancy rates within the population.^9^

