#### Contraceptive use at 4 months

This will be based on self-reported data from women at a telephone follow-up interview with a research nurse at 4 months after obtaining EC. If participants prefer, the questions can be self-completed by a web-based questionnaire or paper questionnaire sent by the post. Women will be asked what method of contraception they are using (if any), if they attended a GP or SRH service for this, if they used the POP (intervention phase only) and their pregnancy status. If pregnancy has occurred since EC then the validated London Measure of Unintended Pregnancy tool will be administered to measure intended-ness of the index pregnancy^20^ (table 1).

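### The economic decision rule prices abortion as the only consequence of pregnancy, so averted unintended births add nothing to the saving, although Table 1 defines the outcome per pregnancy prevented

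*Protocol article*

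**What the plan says.** The Economic evaluation section of the protocol article takes the perspective of the health system and then itemises costs by arm. For control: "In the control arm, the costs are (1) cost of EC, (2) cost of pharmacist provision of EC, (3) cost of abortions". The intervention arm has these plus ("4) the cost of the POP, (5) cost of pharmacist training to provide POP and (6) cost of pharmacist provision of POP"). The first two items are treated as equal between arms, and the extra cost of the intervention is the sum of the last three.

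The result is to be worded as follows: "for every £100 spent on the intervention results in x fewer abortions for a savings of £Y". The decision rule comes next: "If Y is greater than 100 then the intervention is cost-effective". The only sensitivity analysis named varies items 4, 5 and 6, which are the costs of supplying the POP.

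Three other places bear on this:
- The Introduction states: "Unintended pregnancy also ends in childbirth; around 10% of UK births are unintended and 25% mistimed". It also puts the NHS cost of unintended pregnancy, not of abortion alone, at over £1 billion a year.
- Table 1, under Outcomes, gives the economic outcome as an ICER with pregnancies prevented as its unit of effect.
- The section on contraceptive use at 4 months collects pregnancy status and its intendedness: "If pregnancy has occurred since EC then the validated London Measure of Unintended Pregnancy tool will be administered".

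**The concern.** The intervention acts by preventing unintended pregnancies. Some of those would have ended in abortion and some in birth, and the health system pays for both. The written rule credits the intervention with the first kind only.

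This is a stated rule, not a detail left for a fuller plan: the article fixes the cost items, the unit of effect, the formula for the saving and the threshold. Its unit of effect (abortions) also differs from the one in Table 1 (pregnancies).

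Cost-effectiveness is a listed secondary outcome, and the Discussion links it to possible NHS savings. A yes/no threshold applied to an understated saving can give the wrong answer near the threshold. The planned sensitivity analysis could not show this, because it varies only delivery costs.

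**Working it through.** The article gives no unit costs and no numerical result (x and Y are symbols), so there is no figure to reproduce. The check is algebraic, followed by an illustration.

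**Formula.** Let A be the abortions averted per £100 spent, c the NHS cost of an abortion, b/a the unintended births averted per abortion averted, and r the NHS cost of a birth divided by that of an abortion.

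- As written: Y = A × c.
- With births priced: Y_full = A × c + A × (b/a) × r × c = Y × F, where F = 1 + (b/a) × r.

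F exceeds 1 whenever b/a and r are positive, so Y is below the full gross saving if any averted pregnancy would have ended in birth.

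**Inputs from the Introduction.** Almost 200 000 abortions in 2017; about 10% of UK births unintended and 25% mistimed.

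**Assumptions not in the article.** 600 000 to 800 000 UK births a year; r from 0.5 to 4; averted pregnancies split between birth and abortion as in the population.

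**Results.** b/a = births × share ÷ 200 000. The uncosted share of averted outcomes is (b/a) ÷ (1 + b/a).

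| Births counted | Births per year | b/a | Uncosted share | F, r = 0.5 | F, r = 1 | F, r = 2 | F, r = 4 |
|---|---|---|---|---|---|---|---|
| Unintended (10%) | 600 000 | 0.30 | 23% | 1.15 | 1.30 | 1.60 | 2.20 |
| Unintended (10%) | 800 000 | 0.40 | 29% | 1.20 | 1.40 | 1.80 | 2.60 |
| Plus mistimed (35%) | 600 000 | 1.05 | 51% | 1.52 | 2.05 | 3.10 | 5.20 |
| Plus mistimed (35%) | 800 000 | 1.40 | 58% | 1.70 | 2.40 | 3.80 | 6.60 |

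The lowest value is 1 + 0.30 × 0.5 = 1.15. The highest for unintended births alone is 1 + 0.40 × 4 = 2.6. With every mistimed birth counted as averted, the top is 1 + 1.40 × 4 = 6.6.

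**Effect on the threshold, saving side only.** Y_full reaches £100 when Y = 100 ÷ F. That is £87 (100 ÷ 1.15) down to £38 (100 ÷ 2.6) for unintended births, and £66 down to £15 if all mistimed births are added.

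**Cost side.** Items 4 to 6 leave out the rapid-access visits to the sexual and reproductive health (SRH) service, and the contraception supplied there, although the Intervention section makes the offer of access part of the intervention. If costing these multiplied the spend by G, the complete figure would be Y × F ÷ G. The article gives nothing from which to set G, so whether F ÷ G lies above or below 1 is unknown.

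**The case against.** The strongest reply is that the cost list need not be exhaustive. The same section says, in general terms, that direct and indirect health service use will be costed, and it plans a decision model for costs and benefits after the trial. Most births from conceptions during follow-up would fall in that later period, and a condensed article may leave model branches to a fuller plan. This stands in part: a reader might infer that births are excluded from the whole evaluation, and the article does not establish that. But neither statement mentions births or maternity care, and neither enters the itemised list or the £100 rule. If births are intended, the section needs reconciling with itself and with Table 1.

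A second reply is that counting only registry-verified abortions is a cautious base case. That is reasonable for a base case, but the article presents it as the sole basis of a yes/no verdict.

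Three stronger readings are tempting and not supported:
- That a worthwhile intervention will be reported as not cost-effective. The omitted SRH visits and contraception understate the cost of the intervention and pull the other way, so the net direction is open.
- That miscarriage costs are wrongly left out. The article does not mention miscarriage.
- That "The costs (1) and (2) are the same in both groups" is wrong because of repeat emergency contraception (EC) during follow-up. The sentence reads naturally as the EC supplied to every participant at recruitment, and nothing in the article points to differing repeat use.

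**Conclusion.** The point holds for the gross saving. Under the written rule an averted unintended birth is worth £0, which fits neither the health-system perspective, nor the Introduction, nor the unit of effect in Table 1. The direction of the bias in Y follows from the algebra, provided that the intervention averts at least some pregnancies that would have ended in birth.

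The size cannot be derived from the article. A factor of about 1.15 to 2.6 is an illustration resting on the assumed birth numbers, cost ratio and population split; women who have just sought EC may divide differently between abortion and birth. The figure of 6.6 is an upper range, because some mistimed births are postponed and not avoided. No conclusion follows about the net cost-effectiveness result. The primary outcome is unaffected. The change should be made before the economic analysis is run.

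**What to change.** 1. Reconcile the Economic evaluation section with Table 1 by expressing the ICER per unintended pregnancy prevented.
2. Add to the planned decision model a branch and a unit cost for unintended pregnancies that continue to birth, with a stated, assumed split of pregnancy outcomes.
3. Report Y and the £100 rule with and without this branch.
4. Extend the sensitivity analysis from items 4 to 6 to the outcome split and the cost of a birth.

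Use the pregnancies reported at 4 months only as a supporting check. They cover 4 months against 12 for registry abortions, and responders only, with 25% expected not to provide 4-month data. The items described are pregnancy status and intendedness, not how the pregnancy ended.

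The cost is wording in the economic plan, one unit cost and one model branch, with no new participant data. The downside is that the added item rests on assumed inputs, which is why both versions should be shown.

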### Intervention

The planned intervention is a composite intervention. Each woman in the intervention phase will receive 3 months of POP (in a single package covering 3 months) and an invitation to attend a local participating SRH service to discuss and obtain effective contraception (including LARC methods). Three packets of POP, (75 mcg desogestrel; UK) containing 28 tablets each will be provided at no cost to women as a bridging method of contraception, providing them with 3 months of contraception during which time they can get an appointment with a contraceptive provider to obtain their preferred method of contraception. Locally approved patient group directions (ie, strict criteria to permit provision of specified medicines by non-prescribers) will permit participating pharmacists to dispense the POP to women recruited to the study. Prestudy training will be undertaken with participating pharmacists including identifying medical contraindications to POP, potential drug interactions medications and ‘missed pill’ guidance for POP. Pharmacists will advise women to start the POP the day following intake of EC^10^ and provide women with a patient information booklet on the POP from the family planning association (www.fpa.org).

Pharmacists will encourage women to attend the participating local SRH service to obtain the contraceptive method of their choice. Participants (intervention phase) will be given a study card to alert staff at SRH services that they are in the Bridge-It study and should be seen as a drop in for contraception that same day. This card will also provide written information about the location and opening hours of the local participating SRH service. These SRH services are within a 5 mile radius of the participating pharmacies and provide all methods of contraception at no cost as is the norm in the NHS.

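### The economic evaluation promises to cost health service use, but its incremental-cost formula leaves out the clinic visits and methods that rapid SRH access is meant to generate

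*Protocol article*

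**What the plan says.** All the costing rules are in the Economic evaluation section of the protocol article.

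- Perspective: "The overall perspective used will be that of the health system".
- General scope: "Costs will include the pharmacist training to provide POP, direct and indirect costs of health service use, and the provision and dispensing of POP".
- Control-arm list: "In the control arm, the costs are (1) cost of EC, (2) cost of pharmacist provision of EC, (3) cost of abortions".
- Items added for the intervention arm: "4) the cost of the POP, (5) cost of pharmacist training to provide POP and (6) cost of pharmacist provision of POP".
- Incremental cost: "so the extra cost of the intervention will be the sum of (4), (5) and (6").

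The section then expresses the result as savings of £Y for each £100 spent on the intervention and calls the intervention cost-effective when Y exceeds 100. The sensitivity analysis varies items 4, 5 and 6.

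The Intervention section describes a composite. Besides the three-month pill supply, each woman receives "an invitation to attend a local participating SRH service to discuss and obtain effective contraception (including LARC methods"). It adds that these services supply every method free to the woman, as is usual in the NHS.

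**The concern.** The general scope sentence and the formula cannot both be followed. The scope sentence covers contraceptive attendances and clinic-supplied methods. The formula and the two numbered lists contain neither, and the only later care they include is abortion.

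The gap falls on the second component of the intervention. SRH visits and methods, including LARC, are NHS costs under the chosen perspective, and the intervention is designed to increase them. Abortions averted over 12 months are credited to the intervention, including any averted by a method fitted at the clinic. The cost of that method is not charged to it. Because the sensitivity analysis is confined to items 4 to 6, it cannot reveal the gap.

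At stake is the cost-effectiveness statement, which the Discussion links to possible savings for the NHS.

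**Working it through.** The article gives no unit cost, abortion rate or cost-effectiveness ratio, so there is no stated figure to reproduce. The check is algebraic, followed by an illustration.

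**Definitions, per woman**
- X = (4) + (5) + (6), the article's incremental cost.
- S = savings from fewer abortions, the between-arm difference in item (3).
- D = net between-arm cost of GP/SRH contraceptive attendances and methods supplied (intervention minus control).

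**Decision rule**
- As stated: Y = 100 × S / X, so Y > 100 exactly when S > X.
- With visits and methods included (and X + D > 0): Y = 100 × S / (X + D), so Y > 100 exactly when S > X + D.
- If D > 0, any S between X and X + D is called cost-effective when it is not.
- If D = 0, the two rules agree.
- If D < 0, any S between X + D and X is wrongly called not cost-effective.

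**Which sign the article implies.** The Sample size calculation section assumes effective use of 30% in control and 45% with the intervention, a difference of 15 points. The Pilot section explains that 4 months was chosen because the pharmacy supply will have run out by then. The planned gain should therefore come largely from methods obtained from a provider, which items (4) to (6) do not cover. That points to D > 0.

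**Illustration only.** Assumed values, not in the article: a visit plus method costs c = £50 to £150, and X = £20 to £40. Let d be the between-arm difference in the proportion of women who use a visit and method. Then D = d × c, and the ratio of full to stated incremental cost is (X + D) / X.

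| d | D | Smallest ratio | Largest ratio |
|---|---|---|---|
| +15 points | £7.50 to £22.50 | (40 + 7.50)/40 = 1.19 | (20 + 22.50)/20 = 2.13 |
| +5 points | £2.50 to £7.50 | (40 + 2.50)/40 = 1.06 | (20 + 7.50)/20 = 1.38 |
| 0 | £0 | 1.00 | 1.00 |
| −5 points | −£7.50 to −£2.50 | (20 − 7.50)/20 = 0.63 | (40 − 2.50)/40 = 0.94 |

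For example, with X = £20 and D = £7.50, abortion savings between £20 and £27.50 per woman pass the stated rule but do not cover the full cost.

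**Data to close the gap.** The Contraceptive use at 4 months section asks women for their current method and "if they attended a GP or SRH service for this". The Validation section obtains, for both phases, attendance at the participating SRH service and the method received.

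**The case against.** The strongest reply is that nothing has been left out: health service use is in scope by the general sentence, the numbered formula is a simplified exposition, and a condensed article may leave the cost inventory to a fuller document. A missing inventory would indeed be no fault. But the article does give one, equates the extra cost with three named items, and builds both the decision rule and the sensitivity analysis on them. What stands is that this is a contradiction within one section, not a settled decision to exclude clinic costs.

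A reader might also infer that the cost-effectiveness result is biased in favour of the intervention, by a known and large amount. The article does not support that.

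- Only the net difference matters. Control women are advised to attend a provider, 30% are assumed to be using effective contraception, and their visits and methods are uncosted too.
- The intervention arm is charged for the whole bridging supply, while no contraceptive supplied to controls is charged. The three-month supply could also delay or replace some visits.
- Only abortions count as savings, although the Introduction says unintended pregnancy also ends in childbirth and is costly to the NHS. That omission works against the intervention.
- The 15 points are a difference in use at 4 months, not in visits or newly supplied methods. Some users may still be taking the pharmacy pill, already counted in item (4).

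These points make the direction conditional and leave the size unknown. They do not make the formula agree with the scope sentence.

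**Conclusion.** The point holds as an internal contradiction with a likely, conditional consequence. Followed literally, the formula gives a wrong incremental cost whenever visits and methods differ in cost between arms. Under the trial's own hypothesis the expected error is an understatement, and the error in the conclusion is confined to abortion savings between X and X + D.

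The size cannot be derived from the article. The ratios of 1.19 to 2.13 at 15 points rest wholly on assumed unit costs and on treating the planned difference in use as a difference in visits and methods. They show that the gap could matter and do not estimate it.

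The economic evaluation is a secondary outcome (Outcomes, Table 1), and the primary analysis and sample size are untouched. This is something that should be fixed before the analysis; it does not threaten the trial.

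**What to change.** Reconcile the scope sentence with the formula.

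1. Define incremental cost as the between-arm difference in total NHS cost per woman, and base the £100/£Y statement on it.
2. Add two items to the cost lists of **both** arms: GP/SRH contraceptive attendances, and contraceptive methods supplied there, including LARC and its fitting. Use the 4-month questionnaire and the SRH validation data.
3. State the assumptions these data require. The article does not say that the number of visits is recorded. The validation data cover only participating SRH services, so GP and other supply rests on self-report, with 25% non-response assumed at 4 months. Self-reported use stops at 4 months while abortions are counted to 12, so say how use between 4 and 12 months is handled, so that costs and savings share one horizon.
4. Extend the sensitivity analysis to the two new items and to these assumptions.

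The cost is some extra costing work and unit-cost sourcing, using data that are largely collected already, with no change to trial conduct. The result may be less favourable to the intervention.

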**Methods and analysis:**

Bridge-It is a pragmatic cluster randomised cohort cross-over trial designed to determine whether pharmacist provision of a bridging supply of a progestogen-only pill (POP) plus rapid access to a local SRH clinic, results in increased uptake of effective contraception and prevents more unintended pregnancies than provision of EC alone. Bridge-It involves 31 pharmacies in three UK regions (London, Lothian and Tayside) aiming to recruit 626–737 women. Pharmacies will give EC (levonorgestrel) according to normal practice and recruit women to both intervention and the control phases of the study. In the intervention phase, pharmacists will provide the POP (desogestrel) and offer rapid access to an SRH clinic. In the control phase, pharmacists will advise women to attend a contraceptive provider for contraception (standard care).

Women will be asked 4 months later about contraceptive use. Data linkage to abortion registries will provide abortion rates over 12 months. The sample size is calculated on the primary outcome of effective contraception use at 4 months (yes/no) with 90% power and a 5% level of significance. Abortion rates will be an exploratory secondary analysis. Process evaluation includes interviews with pharmacists, SRH clinicians and women. Cost-effectiveness analysis will use a healthcare system perspective and be expressed as incremental cost-effectiveness ratio.

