### Outcomes

A full list of study outcome measures is included in table 1. Outcomes at 4 months will primarily be collected via telephone interviews or via web-based questionnaires. However, participants will also have the option to provide the same information by a postal questionnaire. The primary outcome is use of effective contraception at 4 months (intervention vs standard care).

**Table 1 T1:** Study outcomes

	Data source
Main outcome	
Use of effective contraceptive method (hormonal or intrauterine) in intervention versus control at 4 months	Self-reported (telephone or self completed survey) at 4 months
Secondary outcomes	
Numbers undergoing an abortion within 12 months intervention versus control	National abortion registries
Economic evaluation	Incremental cost-effectiveness ratio for pregnancies prevented

Secondary outcomes are proportion of participants having an abortion within 12 months of EC use using record linkage from participants to national registries and cost-effectiveness.

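### The Y > 100 rule tests for cost saving, not for an acceptable cost-effectiveness ratio, and its effect unit (abortions) conflicts with Table 1 (pregnancies prevented)

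*Protocol article*

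**What the plan says.** The protocol article describes the economic result in three places.

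- **Abstract, Methods and analysis:** "Cost-effectiveness analysis will use a healthcare system perspective and be expressed as incremental cost-effectiveness ratio". The same paragraph says of the outcome that drives the savings: "Abortion rates will be an exploratory secondary analysis".
- **Outcomes, Table 1:** the economic entry is "Incremental cost-effectiveness ratio for pregnancies prevented". The text below the table makes cost-effectiveness one of the two secondary outcomes.
- **Economic evaluation:** "We can then state the outcome as conventional incremental cost-effectiveness ratio". The section then explains this as "for every £100 spent on the intervention results in x fewer abortions for a savings of £Y" and adds the rule "If Y is greater than 100 then the intervention is cost-effective". The extra cost of the intervention is the pill, the training and the pharmacist's provision of the pill (items 4 to 6). The stated sensitivity analysis is "We will examine the sensitivity of the outcomes to variations in the costs of 4, 5 and 6". A decision model is to follow the trial-based analysis, with no detail given.

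**The concern.** An ICER is the difference in cost divided by the difference in effect. It is judged against what the payer would give for one more unit of effect. The rule as written compares savings with spending and contains no such value. It therefore answers whether the intervention pays for itself, under a label that belongs to another question. The Discussion keeps the two ideas apart, since it presents NHS savings as something that could follow if the intervention is cost-effective.

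The second problem is the denominator. Abortions averted and pregnancies prevented are different quantities: the Introduction says that unintended pregnancy also ends in childbirth. A ratio per abortion averted and a ratio per pregnancy prevented would differ for the same trial data, and the article commits to both.

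At stake is the conclusion on a declared secondary outcome. The primary outcome, its analysis and the sample size are not affected.

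**Working it through.** The threshold is a rule and not a derived figure, so there is no number to reproduce. The check is algebra, followed by an illustration.

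**Inputs from the Economic evaluation section**
- Extra cost per woman, dC: the sum of items 4, 5 and 6. No value given.
- Cost per abortion, C: the same in both arms. No value given.
- Abortion risk reduction, RD: control minus intervention over 12 months. No rate given.

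**What x and Y are**
- £100 pays for 100/dC women, so x = 100 × RD/dC abortions averted.
- The saving is Y = x × C = 100 × RD × C/dC.

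**What the rule tests**
- Y > 100 holds exactly when RD × C > dC, that is, when dC − RD × C < 0.
- dC − RD × C is the net incremental cost per woman, so the rule tests whether it is negative.

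**What the ICER is**
- ICER = (dC − RD × C)/RD.
- In the article's own quantities, (100 − Y)/x = (100 − 100 × RD × C/dC)/(100 × RD/dC) = (dC − RD × C)/RD, the same thing.

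**Reading the result by range of Y**
- Y > 100: requires RD > 0, so the intervention is cheaper and averts abortions. It dominates on the counted costs.
- 0 < Y < 100: the ICER is positive and finite. Whether it is acceptable depends on a value per unit of effect. The rule is silent.

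**Illustration (assumed dC = £30, C = £1,000)**

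| RD | x per £100 | Y | Net cost per woman | ICER per abortion averted |
|---|---|---|---|---|
| 1% | 0.033 | 33 | £20 | £2,000 |
| 2% | 0.067 | 67 | £10 | £500 |
| 4% | 0.133 | 133 | −£10 | −£250 (dominant) |

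For example, at RD = 2%: Y = 100 × 0.02 × 1,000/30 = 67, and (100 − 66.7)/0.0667 = £500.

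The rule is met only when RD > dC/C, here 30/1,000 = 3 points. With dC from £15 to £60 and C from £500 to £1,000, this break-even runs from 15/1,000 = 1.5 points to 60/500 = 12 points. All these costs are assumptions.

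**Effect unit, side by side**
- Table 1: pregnancies prevented.
- Economic evaluation: x counts abortions, and abortions are the only pregnancy outcome among the listed costs.
- Introduction: unintended pregnancies end in births as well as abortions, so one unit cannot stand in for the other.

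**The case against.** The strongest defence is that the rule says if, not only if. It gives a sufficient condition, and the algebra confirms that it is sufficient on the counted costs. No verdict is stated for Y below 100. The article also reports x alongside Y, and the two together yield the net ICER, so no information is lost. This stands, and it limits the point to a mislabelled measure and a threshold that covers only part of the range. It does not rescue the label, because neither Y nor the break-even test is a conventional ICER. Nor does it touch the clash of effect units.

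A reader might infer three stronger things that the document does not support.

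- **That the economic conclusion would be wrong.** It would be wrong only if the rule were used as the sole criterion and the result fell between 0 and 100. The article does not say that it will be used that way.
- **That the rule will be applied to a bare point estimate.** The article does not say so. Bootstrap intervals, probabilistic analysis or acceptability curves are commonly left to a fuller plan, and the unspecified decision model may also deal with uncertainty.
- **That the rule would often declare success by chance.** Any such probability needs abortion rates and costs that the article does not give. For instance, with 313 to 368 women per arm, an assumed abortion risk of 4–10%, no true effect and clustering ignored, the chance that Y exceeds 100 is about 0.15–0.27 at a 1.5-point break-even, but below 0.01 at 6 points. A figure that moves this far with the assumptions is not evidence against the rule.

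**Conclusion.** The point holds on two counts, both visible in the text. First, the only stated threshold for cost-effectiveness is the condition for negative net cost, although the measure is called a conventional ICER. This rests on algebra alone and needs no assumed values. Second, the effect unit is abortions in the Economic evaluation section and pregnancies prevented in Table 1.

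The practical risk is one-sided: an intervention that costs the NHS something per abortion averted, but an acceptable amount, has no route to a positive finding under the stated rule. How likely that is cannot be computed from the article. The illustration shows only that the gap between an abortion reduction above zero and the cost-saving point could be anywhere from 1.5 to 12 points under the assumed costs.

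The stated sensitivity analysis adds a smaller weakness. Y is proportional to RD, yet the analysis names only costs 4 to 6, and RD comes from an outcome that the Abstract calls exploratory.

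**What to change.** - **One effect unit** in Table 1 and the Economic evaluation section. Abortions averted over 12 months, from registry linkage, is the simplest. It avoids mixing 12-month linked data with 4-month self-report, for which 25% missing data are expected. Births would then lie outside the unit, and the report should say so.
- **The ICER as such:** the difference in NHS cost per woman divided by the difference in that effect, equivalently (100 − Y)/x. Show the cost and effect differences beside it, because a negative ratio cannot be read alone.
- **Relabel Y > 100** as cost-saving and report it as a separate result.
- **Extend the sensitivity analysis** from costs 4, 5 and 6 to the abortion difference, for example across its confidence interval from the planned hierarchical analysis.

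The cost is a change of wording in two places and one further sensitivity analysis on data already to be collected. The economic message becomes slightly less simple than pounds saved per £100 spent.
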